## Abstract

**Background:**

Pediatric obesity is a serious, but clinically neglected, chronic health problem. Despite the high prevalence, excess weight problems are rarely managed when children attend clinical services. It is recommended that obesity treatment uses a “chronic-care” approach to management, with different types and intensity of treatment dependent upon severity of obesity. There are several new secondary and tertiary weight management services being implemented within New South Wales (NSW), Australia in 2017/2018 with differing models of care. This study will ascertain what factors affect acceptability, reach, and participation, as well as measure the clinical effectiveness of these services.

**Methods:**

This is a acceptability and effectiveness study building upon existing and planned secondary and tertiary level service delivery in several health districts. This study will recruit participants from seven different pediatric weight management services (PWMS) across five Local Health Districts in NSW, Australia. Using a mixed-methods approach we will document a range of process, impact and clinical outcome measures in order to better understand the context and the effectiveness of each PWMS model. The project development and implementation is guided by the Theoretical Domains Framework. Participants will include parents of children less than 18 years of age attending PWMS, clinicians working as part of PWMS and health service managers. Data will be captured using a combination of anthropometric measures, questionnaires, one-on-one semi-structured interviews and focus groups.

**Discussion:**

Results from this study will assess the acceptability and effectiveness of different models of care for pediatric weight management. Such information is required to inform long-term sustainability and scalability of secondary and tertiary care services to the large number of families with children above a healthy weight.

## Background

Pediatric obesity is a serious, but clinically neglected, chronic health problem. In Australia one in four school-aged children and adolescents is affected by overweight [1] or obesity (6% with obesity, a further 2% with severe obesity) [2]. Pediatric obesity is associated with a range of immediate and longer-term health problems [3]. Despite the high prevalence, excess weight problems are infrequently managed when children attend clinical services [4, 5]. Barriers to weight management by health professionals include: difficulty raising the issue, uncertainty about advice to offer and referral pathways, and lack of local service capacity [5, 6].

Untreated, the natural history of obesity in children and adolescents will worsen over time [7]. The American Academy of Pediatrics recommends that obesity treatment uses a “chronic-care” approach to management, with different types and intensity of treatment dependent upon severity of obesity [8]. Family-based lifestyle interventions incorporating behavior modification around eating and activity are effective and considered first-line treatment for pediatric obesity [3, 9, 10], especially in younger children [11]. Although there is a central role for primary care physicians and other health professionals, including nurses and dietitians, in the management of childhood overweight and obesity [12], there is also a need for specialist secondary and tertiary care services for those with more severe obesity [3]. Primary, secondary and tertiary care services can all provide dietary modification, advice about exercise and physical activity [12], medical management of obesity-associated complications, family-based lifestyle changes and behavior modification techniques [3]. Secondary and tertiary services differ from primary care services by providing more intensive services within a multi-disciplinary team environment and for children with more severe obesity.

Australia has a publicly funded healthcare system [13]. The individual states and territories are responsible for managing hospital and community services [14]. Primary care is the first contact with the health system and does not include hospital services. Secondary care services are provided by specialist care providers and are a direct link between primary and tertiary services. Within New South Wales the state is divided into eight metropolitan local health districts (LHDs) and seven rural LHDs. In addition, there are two specialist networks, including the Sydney Children’s Hospitals Network (SCHN).

There are limited pediatric obesity services in Australia, including in the state of NSW. Prior to 2017, the number of services available in the secondary and tertiary setting had not changed in the previous ten years [15], despite the number of children with severe obesity significantly increasing. The few existing services are poorly linked, with no well-established models of care or healthcare pathways across primary, secondary or tertiary care networks. Adequate treatment strategies for childhood obesity will require changes in healthcare delivery systems [16].

Several LHD’s within NSW are implementing new services to deliver integrated weight management programs for children and adolescents. The new and existing services vary greatly in their models of care, depending upon local resourcing, clinical needs, staff expertise and patient characteristics. We have a unique opportunity to research the implementation and integration of these pediatric weight management services (PWMS) alongside established services to determine the acceptability, clinical effectiveness and impact of the services. There is limited research assessing the effectiveness of interventions in clinical practice for children with obesity [17] . Inadequate documentation and poor retention rates of patients are factors shown to prevent the assessment of “real-world” models of care for PWMS in international settings [17]. No such research has been undertaken previously in Australia.

### Primary objective

To assess the acceptability, reach, participation rates and retention rates of different models of care for management of childhood obesity at the secondary and tertiary level care.

### Secondary objectives

To compare the clinical effectiveness of the different models of care for the management of childhood obesityTo assess the impact of the different pediatric weight management models of care on weight-related behaviors (eating, physical activity and sedentary behaviors).To determine the costs and cost-effectiveness of the different models of care from a health provider and consumer perspective.

## Methods/design

We have designed a multi-perspective, concurrent, mixed-methods study testing the appropriateness, acceptability, clinical effectiveness, and impact of secondary and tertiary level PWMS. It will harness the opportunity provided by the development of new PWMS in the state of NSW in 2017/2018 (a “natural experiment”). Qualitative and quantitative approaches will be used to gather evidence and assess the existing and new models of care. We will document a range of process, impact and clinical outcome measures in order to better understand the context and the effectiveness of each child and family weight management service model. Health economic evaluation of different models of care will also be undertaken.

The research will be guided by the Theoretical Domains Framework [18]. A co-design framework and Linkage-Exchange Model will be applied throughout this project [19]. This will ensure that patients, families, clinicians and managers are engaged in the project at all stages of development and that a systematic and theoretically underpinned model is used to disseminate findings into practice and policy [19]. Linkage and exchange strategies involve initiatives that seek to i) promote research use in decision contexts, and ii) encourage research that generates evidence that is of use to decision-makers. Interpersonal connections (interactions) between clinicians, managers, patients/families are vital in this process.

### Study setting

The study will be undertaken at six secondary level care clinics and one tertiary clinic for child weight management. These clinics are limited to children less than 18 years of age and their families. Each clinic uses a different model of care with a combination of face-to-face and group education sessions within a multi-disciplinary team.

### Study activities

Parts 1, 2 and 3 of the study will address the following objectives:

Primary Objective: To assess the acceptability, reach, participation rates and retention rates of different models of care for management of childhood obesity at the secondary and tertiary level care.

### Part 1: Assessment of parent/ guardian views of the acceptability of the secondary weight management service

In part 1 of the study we will utilize a cross-sectional assessment of parent acceptability, satisfaction with the PWMSand burden on the family attending the services determined by a questionnaires and one-on-one interviews. Participants will be recruited at completion of the weight management program or at three months into the program for those attending programs with a longer follow-up.

#### Participants

Parents/carers of a child who has been attending secondary weight management service and are fluent in English will be included in this study.

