#### Participants

Participants will be clinicians who are involved with the care of patients in a secondary or tertiary PWMS. Clinicians will include pediatricians, dietitians, nurses, psychologists and physiotherapists. Clinicians will be given a patient information sheet and written consent will be obtained before taking part on the study.

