#### Participants

As part of the questionnaire developed for Part 1 of the study (consented) parents/carers will be asked about their time inputs as they navigate the care pathway e.g. time to attend consultations and travel time, type of services used, including specialist services and use of organised programs.

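### The Part 1 parent criterion names only secondary services, contradicting the study's two-level scope; applied literally, it leaves the one tertiary model without parent-reported data

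*Protocol article*

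**What the plan says.** All references are to the protocol article.

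- **Part 1, Participants.** "Parents/carers of a child who has been attending secondary weight management service and are fluent in English will be included in this study". The Part 1 heading has the same scope: "Assessment of parent/ guardian views of the acceptability of the secondary weight management service".
- **Primary objective.** Acceptability, reach, participation and retention are to be assessed for "different models of care for management of childhood obesity at the secondary and tertiary level care". Under Study activities this objective is given to three parts jointly: "Parts 1, 2 and 3 of the study will address the following objectives".
- **Study setting.** "The study will be undertaken at six secondary level care clinics and one tertiary clinic for child weight management". The same section says that no two clinics share a model of care.
- **Abstract, Methods.** Recruitment is from seven services, and the parents are described by their child's age and attendance at a weight management service, with no restriction by level.
- **Part 2, Participants.** "clinicians who are involved with the care of patients in a secondary or tertiary PWMS". Part 3 sets the same two-level scope for health service managers.
- **Part 4, Participants.** All children attending the clinics.
- **Part 5, Participants.** Parents' time inputs and service use are collected "As part of the questionnaire developed for Part 1 of the study".

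**The concern.** Part 1 is the only part that collects parents' views, and its eligibility sentence names one of the two levels of care that the study sets out to describe. Eligibility sentences decide who is approached. The Part 1 Recruitment section confirms this: site investigators identify those who meet the inclusion criteria, and the project officer approaches them.

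At stake is the parent component of the primary objective for the tertiary model. The Part 4 Data analysis section plans to compare parental satisfaction between models of care. If the criterion is followed literally, that comparison has an empty cell for the tertiary clinic. The empathy measure, the treatment-expectations tool, the accessibility questions and the telephone interviews would be missing there too. The loss may be hard to repair later, because Part 1 is cross-sectional: parents are recruited at programme completion, or at three months in longer programmes.

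**Working it through.** There is no statistical figure to reproduce. The 140 questionnaires are stated to be a pragmatic number, with no alpha, power or effect size behind it. The check sets the statements of scope side by side.

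| Place in the protocol article | Level of care covered |
|---|---|
| Abstract, Methods | Seven services; parents not restricted by level |
| Primary objective; Study activities | Secondary and tertiary; assigned to Parts 1, 2 and 3 |
| Study setting | 6 secondary + 1 tertiary = 7 clinics |
| Part 1 heading | Secondary |
| **Part 1, Participants** | **Secondary** |
| Part 2 heading / Participants | Secondary / secondary or tertiary |
| Part 3 heading / Participants | Secondary / secondary or tertiary |
| Part 4 heading / Participants | Secondary / all children at the clinics |

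**Step 1: is the narrow wording only a habit of the headings?** The headings of Parts 1 to 4 all say secondary. In Parts 2, 3 and 4 the participant text then widens the population to both levels or to all clinics. In Part 1 it does not. The heading habit therefore explains the Part 1 heading but not the Part 1 criterion.

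**Step 2: who is admitted on a literal reading?** Parents from 6 of 7 clinics, and none from the tertiary clinic. The share of clinics without parent data is 1/7 = 14%. Because there is only one tertiary clinic, this is 1/1 = 100% of the tertiary level, and one whole model of care.

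**Step 3: which data would be missing for that model?**

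- Part 1 questionnaire: satisfaction, perceived clinician empathy, treatment expectations, and the time and accessibility items.
- Part 1 interviews: these are open only to parents who complete the questionnaire, so the gap carries over.
- Part 5: parents' time inputs and service use, which come from the same questionnaire. These serve the cost objective, which is secondary.

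**Step 4: which data would remain?** Clinician views (Part 2), manager views (Part 3), BMI z-score and behaviours (Part 4), and the health-system costs in Part 5 that rest on health district financial records and standard consultation costs.

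**The case against.** The strongest reply is that the article uses secondary loosely throughout and that tertiary parents were always meant to be included. There is real support for this. The abstract describes the parents without a level. The introduction to Part 1 refers to the weight management service in general. The Recruitment section speaks of each site and says that the 140 reflects the potential participants from each clinic. The criterion contains no word such as only and no explicit exclusion. This stands as an account of the likely intention. It does not remove the conflict, because the criterion is the text that recruitment is told to follow, and Part 1 is the one part that does not widen its population there.

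A reader might also draw stronger conclusions that the documents do not support:

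- **Deliberate exclusion of tertiary families.** The abstract points the other way. What the text shows is a contradiction.
- **A primary objective that includes family costs.** It covers acceptability, reach, participation and retention. Costs fall under a secondary objective.
- **No out-of-pocket cost data for the tertiary model.** Part 5 ties only time inputs and service use to the Part 1 questionnaire. It lists out-of-pocket and productivity costs without naming their source, so their loss is an inference.
- **Loss of a planned test of secondary against tertiary care.** None is planned; the comparison is between models of care. With one tertiary clinic, level and clinic could not be separated anyway.
- **A change in the number recruited per clinic.** Equal division would give 140/7 = 20 or 140/6 = 23.3, but the article states no split. These averages measure neither bias nor loss of precision.

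**Conclusion.** The Part 1 criterion and heading contradict the abstract, the primary objective, the study setting and the participant criteria of Parts 2 and 3, and they need to be reconciled before sites recruit from them. If the criterion is applied as written, one of seven clinics, which is the whole tertiary level and one distinct model of care, contributes no parent-reported data to the primary objective or to the comparison of parental satisfaction between models. It also lacks the parent time and service-use inputs for Part 5.

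This size rests on two assumptions: that sites apply the sentence literally, and that no other parent-level source exists for those inputs, since the article names none. The mismatch in the wording is certain; whether tertiary parents would actually go unrecruited is not. The gap is confined to parent-reported data at one clinic and does not prevent the study from describing the tertiary service by its other sources. It still matters, because it decides who is enrolled and because how acceptable each model is to families is a central part of the primary objective.

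**What to change.** Amend the Part 1 Participants sentence and the Part 1 heading so that both name a secondary or tertiary service, in line with the criteria in Parts 2 and 3. Recruit parents at all seven clinics within the pragmatic total of 140, without a fixed number per clinic.

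If leaving out tertiary parents was intended, say so and give the reason. Then limit the parent-acceptability and consumer-perspective cost conclusions to secondary services, and adjust the abstract and the statement of what Part 1 contributes to the primary objective.

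The first option costs a short wording amendment and need not raise the total of 140. Its one downside is small: if the 140 was counted over the six secondary clinics alone, including the seventh would leave slightly fewer questionnaires for each secondary clinic. If the 140 already counted all seven, nothing changes.

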#### Quantitative data

Patient satisfaction will be measured using the Short Assessment of Patient Satisfaction Measure [20]. The perception families have of the empathy of their clinician will be measured using the Consultation & Relational Empathy Measure (CARE) [21] which has good reliability, internal consistency and validity [22]. Parental expectation on treatment outcomes will be assessed using a modified version of the Treatment Expectations and Goals Survey Tool [23]. Additional questions, developed by the multi-disciplinary research and clinical team, on time taken to attend appointments, length of appointment and accessibility of the service will be asked using a 5-point Likert scale from “strongly disagree” to “strongly agree”. The multi-disciplinary team included researchers, pediatricians, dietitians, nurses, psychologists and project officers. The questionnaire should take no longer than 20 min to complete.

#### Qualitative data

Parents/ carers who complete the questionnaire will be able to opt-in for one-on-one telephone interviews. Semi-structured telephone interviews will capture parent views on: 1) The acceptability of the service design and delivery (i.e. service location, accessibility, cultural appropriateness, language used, context and acceptability of intervention); 2) perceptions of the services’ strengths and weaknesses; 3) barriers and enablers to attendance at the service and barriers and enablers to behavior change; 4) views on education materials and resources provided by the weight management clinic; and 5) recommendations for improvement. An interview discussion guide has been developed by the multi-disciplinary team based on previous work assessing parental views of weight management services [24, 25].

#### Recruitment

Potential participants who meet the inclusion criteria will be identified by the primary investigators at each site. The project officer will approach the potential participants during their clinic visits and provide the patient information sheet and consent form. If the participant has provided written consent to take part in the study, the project officer will administer the parent questionnaire. At the end of the questionnaire, participants will have the option to consent for the one-on-one interviews.

It is anticipated that a total of 140 participants will complete the parent questionnaire. As this is a non-randomised acceptability study, a formal sample size calculation could not be performed. The number of participants was a pragmatic decision based on the number of potential participants from each clinic during the study timeframe. This pragmatic approach to sample size calculations has been used previously [26] and is within the acceptable range for sample sizes for quantitative analysis in mixed-methods approaches [27].

Consenting participants will then be contacted by phone by the project officer to invite them to participate in a one-on-one interview. Maximum variation sampling will be used to ensure a range of ages, severity of obesity and sex of the children attending the weight management clinics and a range of clinicians to ensure we capture a broad spectrum of perspectives and experiences [28]. The interviews will continue until data saturation is reached with no new themes emerging. It is estimated that 50 families will take part in the one-on-one interviews. These numbers are based on previous studies assessing parent views [29–31].

### Part 2: Assessment of clinician views of secondary services for children who are above their healthy weight range

In part 2 of the study clinician views of the PWMS they work in, the service they provide and their experience working in that service will be assessed by questionnaire and focus groups. The following information will be collected: 1) staffing mix; 2) expertize; 3) training; 4) time commitments; 5) service model; 6) level of multi-disciplinary team work; 7) internal and external department links; 8) costs and funding sources.

#### Participants

Participants will be clinicians who are involved with the care of patients in a secondary or tertiary PWMS. Clinicians will include pediatricians, dietitians, nurses, psychologists and physiotherapists. Clinicians will be given a patient information sheet and written consent will be obtained before taking part on the study.

##### Quantitative data

A questionnaire, developed by the multi-disciplinary research team and clinical team, will be used to capture clinician views about their PWMS. The questionnaire is based on a previously published survey [19]and includes questions on respondent demographics and experience in pediatric weight management, clinic levels of service and demands, weight management service model, approaches to weight management. The questionnaire will take no longer than 20 min to complete.

##### Qualitative data

Focus groups will further explore information gained from the survey and aim to capture: 1) perceptions of service strengths and weakness; 2) barriers and enablers to a successful PWMS; 3) previous experience with non-sustainable services; 4) training needs of clinicians working in pediatric weight management; 5) suggested resources; 5) recommendations for improvement. The semi-structured interview guide for the focus groups was developed by a multi-disciplinary group of researchers and clinicians.

